### Power of the continuous primary outcome

A power analysis for the continuous primary outcome, i.e. a non-verbal cognitive score of PARCA-R, shows that with a sample of 1500 in each group and an expected rate of death of 8%, and a standard deviation of the PARCA score of 18 points, the power will be more than 98% to detect a difference of 3 points (Cohen’s *d* = 0.2 standard deviation), at an alpha of 2.5%.

### Power of the secondary outcomes

For the first secondary outcome, i.e. days alive without mechanical ventilation within the 28 first days of life with a standard deviation of 15 days (unpublished data) and with a minimal clinical relevance difference of 2 days, the power will be 95% at a 5% significance level.

For the other secondary outcome, one or more serious adverse events within the 28 first days of life as described above, assuming a 50% prevalence among mechanical ventilated newborns and a relative risk decrease of 5% in the experimental group, we will be able to detect this difference between the experimental and control group with 78% power at a 5% significance level.

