**Methods/design:**

SafeBoosC-IIIv is an investigator-initiated, multinational, randomised, pragmatic phase-III clinical trial. The inclusion criteria will be newborns with a gestational age more than 28 + 0 weeks, postnatal age less than 28 days, predicted to require mechanical ventilation for at least 24 h, and prior informed consent from the parents or deferred consent or absence of opt-out. The exclusion criteria will be no available cerebral oximeter, suspicion of or confirmed brain injury or disorder, or congenital heart disease likely to require surgery.

A total of 3000 participants will be randomised in 60 neonatal intensive care units from 16 countries, in a 1:1 allocation ratio to cerebral oximetry versus usual care. Participants in the cerebral oximetry group will undergo cerebral oximetry monitoring during mechanical ventilation in the neonatal intensive care unit for as long as deemed useful by the treating physician or until 28 days of life. The participants in the cerebral oximetry group will be treated according to the SafeBoosC treatment guideline. Participants in the usual care group will not receive cerebral oximetry and will receive usual care. We use two co-primary outcomes: (1) a composite of death from any cause or moderate to severe neurodevelopmental disability at 2 years of corrected age and (2) the non-verbal cognitive score of the Parent Report of Children’s Abilities-Revised (PARCA-R) at 2 years of corrected age.

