### Blinding

Clinical staff and parents cannot be blinded due to the nature of the intervention. Thus, the primary outcome will not be blinded in participants relying on parental reporting. If there is no contact with the parents, or if they do not return the questionnaire, data will be collected from health care records. All secondary outcomes will be assessed and reported at 28 days after birth by reviewing the newborn’s health care records. Investigators reviewing the health care records will, if possible, be blinded to the allocated intervention.

Data managers, the steering committee, statisticians, and writers of the two final abstracts (one assuming ‘A’ to be the experimental group and one assuming ‘B’ to be the experimental group) before unblinding of the groups will be blinded. The independent data safety monitoring committee will be provided statistics per allocation group named A and B but can request unblinding.

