### Outcomes

We will use two co-primary outcomes.

First is a dichotomous composite outcome of death from any cause or moderate-or-severe neurodevelopmental disability at 2 years of corrected age. Moderate-or-severe neurodevelopmental disability will be defined as one or more of the following: (1) cerebral palsy with Global Motor Function Classification System level 2 or higher; (2) the Parent Report of Children’s Abilities-Revised (PARCA-R) non-verbal cognitive function score below − 2 standard deviations (SD); (3) hearing loss corrected with aids or worse; or (4) vision impairment defined as moderately reduced vision of one eye, or only being able to perceive light or light reflecting objects, or blind in one eye with good vision in the contralateral eye. This relies on clinical routine data and the parents’ reports relying on their history with the child. The PARCA-R provides a high test–retest reliability and has been used in multiple clinical trials with 2-year follow-up [16].

Second is a continuous outcome comprising the non-verbal cognitive score of the Parent Report of Children’s Abilities-Revised (PARCA-R), a parental questionnaire, at 2 years of corrected age.

We will use two secondary outcomes.

First is days alive without mechanical ventilation within the first 28 days of life.

Second is one or more serious adverse events within the 28 first days of life. Serious adverse events are defined as one or more of the following: death from any cause, any brain injury diagnosed by imaging, seizures treated with antiepileptic medicine, necrotising enterocolitis defined as Bell’s grade 2 or more [17], sepsis defined as confirmed or suspected infection treated with antibiotics for 5 days or more, extracorporeal membrane oxygenation treatment, renal replacement therapy, use of vasopressor/inotropes, nitric oxygen treatment, and on mechanical ventilation at 28 days of life.

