### Sample size

To test a reduction in death or moderate to severe neurodevelopment disability from 20 to 16% between the usual care group versus the cerebral oximetry group (a relative risk reduction of 20%), a total of 1500 participants in each group and a total of 3000 participants is needed. This calculation on the dichotomized, composite primary outcome is based on an alpha level of 2.5% and a power of 73%.

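### The planning SD of 15 days for days alive without mechanical ventilation exceeds the largest SD (14) that a 0–28 day outcome can have; the resulting 95% power is slightly understated

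*Protocol article*

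**What the plan says.** The Outcomes section defines the first secondary outcome: "First is days alive without mechanical ventilation within the first 28 days of life". The section on power of the secondary outcomes plans that same outcome as "days alive without mechanical ventilation within the 28 first days of life with a standard deviation of 15 days", attributes the SD to unpublished data, and pairs it "with a minimal clinical relevance difference of 2 days". It concludes that "the power will be 95% at a 5% significance level".

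The group size comes from the Sample size section: "a total of 1500 participants in each group and a total of 3000 participants is needed". The Blinding section says how the outcome is collected: "All secondary outcomes will be assessed and reported at 28 days after birth by reviewing the newborn’s health care records". No loss of data is assumed for this outcome.

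The article does not describe the unpublished data, and it does not say that 15 was chosen as a deliberately cautious value.

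**The concern.** The outcome has a floor of 0 and a ceiling of 28. The spread of such a variable is limited by its range, and an SD of 15 is beyond that limit. The planning value therefore cannot be the SD of the outcome as the Outcomes section defines it, whatever data it was taken from.

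At stake is the accuracy of one stated planning SD and of the power computed from it. A reader who wants to know how sensitive the trial is on this outcome is given a figure that rests on an impossible input. If the unpublished data are used again in later planning, the same value could be carried forward.

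**Working it through.** **Inputs**

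- Range of the outcome: 0 to 28 days (Outcomes).
- SD: 15 days; difference: 2 days; power 95% at 5% (Power of the secondary outcomes).
- 1500 per group (Sample size), randomised 1:1 (Abstract, Methods/design).
- Assumptions: a two-sided test, since sidedness is not stated, and no missing data.

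**Step 1. Reproduce the stated power.** With SE = SD × √(2/n) and power = Φ(difference/SE − 1.96):

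- SE = 15 × √(2/1500) = 0.548
- 2/0.548 − 1.96 = 1.69
- power = Φ(1.69) = 95.5%

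This agrees with the stated 95%. A one-sided 5% test would give 97.8%, which does not. So the SD of 15 was used in the calculation and is not merely a slip in the text.

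**Step 2. Largest possible SD.** For X between 0 and 28 with mean m, X² ≤ 28X, so the variance is at most 28m − m² = m(28 − m). This is largest at m = 14, where it equals 196. Hence SD ≤ √196 = 14, reached only if half the infants score 0 and half score 28. At any other mean the limit is lower. For assumed means of 18, 20 and 22 days it is √180 = 13.4, √160 = 12.6 and √132 = 11.5 days.

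**Step 3. Can a technicality rescue 15?**

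- Divisor n − 1: for a data set of, say, 500 infants the ceiling is 14 × √(500/499) = 14.01. A sample SD of 15 is attainable only with 6 or fewer infants; with 7 the maximum is already 14.97.
- Counting 29 calendar days: the ceiling is 29/2 = 14.5, still below 15.

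**Step 4. Power with attainable SDs** (difference 2 days, 1500 per group, two-sided 5%). Only the ceiling of 14 follows from the document; the smaller SDs are assumptions.

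| SD (days) | SE | 2/SE − 1.96 | Power |
|---|---|---|---|
| 15 (stated, impossible) | 0.548 | 1.69 | 95.5% |
| 14 (ceiling) | 0.511 | 1.95 | 97.5% |
| 13 (assumed) | 0.475 | 2.25 | 98.8% |
| 12 (assumed) | 0.438 | 2.60 | 99.5% |
| 10 (assumed) | 0.365 | 3.52 | 99.98% |

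**Step 5. Sensitivity to missing data at SD 14.** With an assumed 5% loss (1425 per group) SE = 14 × √(2/1425) = 0.524 and power is 96.8%. With an assumed 10% loss (1350 per group) SE = 0.539 and power is 96.0%. The figure of 97.5% therefore needs its completeness condition stated beside it.

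**The case against.** The strongest case on the other side is that nothing depends on the error. The sample size was set from the dichotomous co-primary outcome. The statistical section rests any claim of superiority on the co-primary outcomes and treats all other results as hypothesis-generating. The power formula was applied correctly, and the input errs on the safe side: no reader is led to think the trial is better powered than it is. All of this stands, and it is why the point is minor. It does not make an SD of 15 possible, and an unseen analysis plan could not do so either.

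Three stronger readings are tempting, and the document does not support them:

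- A reader might infer that 15 is the SD of some other quantity, such as an uncapped duration of ventilation. The article says only that the data are unpublished. A misprint or rounding up would fit as well.
- A reader might infer that mortality of about 8% forces the SD well below 14. It does not do so by itself. Infants ventilated throughout also score 0, and an infant who dies after extubation need not score 0. Arithmetically, 8% deaths at 0, 42% ventilated throughout at 0 and 50% at 28 would still give 28 × √(0.5 × 0.5) = 14, however unlikely that is clinically. The limit depends on the mean, which the article does not give.
- A reader might infer that the 2 days are a misreported detectable difference. The article presents them as the smallest clinically relevant difference, and a smaller SD does not change what is clinically relevant.

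**Conclusion.** The point holds as a minor correction. The stated SD exceeds the mathematical maximum for the outcome by at least one day, and the stated 95% power was computed with it. Power for a 2-day difference is understated by at least about 2 percentage points (97.5% at the ceiling against 95.5% as calculated), and by more if the true SD is smaller. This rests on a two-sided 5% test and complete 28-day data on 1500 per group. The ceiling of 14 needs no assumption beyond the definition of the outcome. The planned sensitivity to 2 days is not threatened under these inputs.

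**What to change.** Check the source of the 15 days. Recompute the SD from the unpublished data on the outcome as defined, scored 0 to 28 with deaths handled as in the outcome definition, and restate the SD and the power.

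Until that is done, replace the sentence with one saying that the SD is at most 14 days and that power for a 2-day difference is about 97.5% or more, assuming complete 28-day data on 1500 per group. Do not name an origin for the 15 days unless the data confirm it.

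The cost is a re-tabulation of existing data and one corrected sentence. No change to sample size, alpha or analysis is needed.

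### The 78% power for the serious-adverse-event outcome does not follow from the stated 5% relative reduction, which gives about 28%; it fits a 5-percentage-point reduction

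*Protocol article*

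**What the plan says.** The section Power of the secondary outcomes in the protocol article gives the second secondary outcome as "one or more serious adverse events within the 28 first days of life as described above". The calculation is made "assuming a 50% prevalence among mechanical ventilated newborns and a relative risk decrease of 5% in the experimental group". The conclusion is that "we will be able to detect this difference between the experimental and control group with 78% power", at a significance level of 5%.

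The number of infants comes from the section Sample size, where "a total of 1500 participants in each group and a total of 3000 participants is needed", and the abstract confirms that they are randomised "in a 1:1 allocation ratio to cerebral oximetry versus usual care". No loss to follow-up is applied to this 28-day outcome. The 20% loss discussed under Challenge 3 concerns the two-year co-primary outcomes.

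The section Sample size also shows how the article uses the word relative: a fall from 20% to 16% is called a 20% relative risk reduction. Challenge 1 uses it in the same way.

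**The concern.** Event rate, effect size, significance level and power are given together, and the group size is fixed two sections earlier. Nothing is left open, so the power can be checked directly. Near a 50% event rate, a 5% relative decrease is only 2.5 percentage points, which is small for 1500 per group. A power close to 80% for so small a difference is implausible at first sight.

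This is one of only two secondary outcomes. It gathers death, brain injury on imaging, seizures, necrotising enterocolitis, sepsis and other events, in a trial whose objective is to weigh benefits against harms. Taken at face value, the sentence makes the trial look sensitive to an effect half as large as the one for which it has 78% power. A reader could then take a neutral result as fair evidence against a 5% relative effect that the trial has little chance of showing.

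**Working it through.** **Inputs**

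- Group size n = 1500 per arm, 1:1 (Sample size; abstract).
- Control rate p1 = 0.50 (Power of the secondary outcomes).
- Effect as written: 5% relative, so p2 = 0.50 × (1 − 0.05) = 0.475.
- Significance level 5%. Sidedness is not stated. I take two-sided as the base case (z = 1.960) and also try one-sided.
- Stated power: 78%.

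**Formula**

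Normal approximation for two proportions, pooled variance under the null:

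power = Φ{ [ |p1 − p2| − z·√(2·p̄(1 − p̄)/n) ] / √([p1(1 − p1) + p2(1 − p2)]/n) }, with p̄ = (p1 + p2)/2.

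**Does the method reproduce the article's other figures?**

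| Outcome | Inputs | Stated | Recomputed |
|---|---|---|---|
| Binary co-primary | 20% vs 16%, 1500 per arm, alpha 2.5% | 73% | 72.9% |
| Binary co-primary, 20% loss | same, 1200 per arm | 62% | 62.1% |
| PARCA-R score | 3 points, SD 18, 1380 per arm (1500 × 0.92), alpha 2.5% | more than 98% | 98.4% |
| Days alive without ventilation | 2 days, SD 15, 1500 per arm, alpha 5% | 95% | 95.5% |

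All four agree (the two continuous outcomes use the corresponding formula for means), so the standard two-sided formulas are the right yardstick here.

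**The effect as written: 50% vs 47.5%**

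- p̄ = 0.4875; null SE = √(2 × 0.4875 × 0.5125/1500) = 0.01825.
- Alternative SE = √((0.25 + 0.249375)/1500) = 0.01825.
- (0.025 − 1.960 × 0.01825)/0.01825 = −0.59; Φ(−0.59) = **27.7%**.

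**A 5-percentage-point effect: 50% vs 45%**

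- p̄ = 0.475; null SE = √(2 × 0.475 × 0.525/1500) = 0.01823.
- Alternative SE = √((0.25 + 0.2475)/1500) = 0.01821.
- (0.05 − 1.960 × 0.01823)/0.01821 = 0.78; Φ(0.78) = **78.3%**.

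Solving the formula for the experimental rate that gives exactly 78% returns 45.0%.

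**Other readings of the sentence**

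| Reading (1500 per arm, two-sided 5% unless stated) | Power |
|---|---|
| 50% vs 47.5%, unpooled variance | 27.8% |
| 50% vs 47.5%, continuity correction | 26.5% |
| 50% vs 47.5%, arcsine | 27.8% |
| 50% vs 47.5%, one-sided 5% | 39.2% |
| 50% taken as the overall rate, relative risk 0.95 | 28.9% |
| 5% taken as a reduction in odds (odds ratio 0.95) | 10.4% |
| 3000 mistakenly entered per arm, two-sided | 49.1% |
| 3000 mistakenly entered per arm, one-sided | 61.5% |

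None comes near 78%.

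**Sample size that 5% relative would need**

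With z for 78% power = 0.772:

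n = [1.960 × √(2 × 0.4875 × 0.5125) + 0.772 × √(0.25 + 0.249375)]² / 0.025² ≈ 5967 per arm, about 11,900 in total. That is about four times the planned 1500 per arm.

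**The case against.** The arithmetic is not in dispute. The best counter-argument is that the power is right and only one word is wrong. Since 78% matches a 5-point absolute decrease almost exactly, and every other power figure in the article reproduces, the calculation was probably done for 50% versus 45% and then described carelessly. On that reading the trial's power is not overstated; the effect is mislabelled, and the figure of 11,900 infants is beside the point. I think this is the more likely explanation, but it remains an inference. Whichever number was meant, the sentence as printed is wrong, and the article's own use of relative elsewhere leaves no looser sense to fall back on.

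A second argument is that little hangs on it. The section Statistical plan and data analysis treats everything beyond the co-primary outcomes as hypothesis-generating, the sample size rests on the composite co-primary outcome, and the section Safety ties no monitoring rule to this figure. That stands, and it limits the consequences to reporting and interpretation.

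Third, a neutral result should be judged from its confidence interval rather than from planning power, and Challenge 1 shows that the authors reason this way. That is fair, and it makes a misreading less likely. It does not justify leaving an incorrect power figure in print.

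**Conclusion.** The concern holds. The stated effect and the stated power are incompatible. For a 5% relative decrease from 50%, power is about 28%, not 78%, an overstatement of about 50 percentage points. The printed 78% belongs to a fall from 50% to 45%, that is, 5 percentage points or 10% relative.

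This rests on 1500 infants per group with complete 28-day data and a two-sided 5% test. Fewer evaluable infants would lower the power further: 25.9% with 1380 per arm and 23.1% with 1200. A one-sided test gives 39.2%. That an absolute difference was labelled as relative is the probable cause, but it is not shown by the article. The primary analyses and the sample size are not touched.

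**What to change.** Decide which effect was intended and make the sentence in Power of the secondary outcomes consistent, in one of two ways:

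- If 5 percentage points was meant: describe the effect as an absolute decrease from 50% to 45% (10% relative) and keep 78%.
- If 5% relative was meant: describe it as 50% to 47.5% and state the power as about 28%.

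In either case, give both event rates and say that the test is two-sided, so that the figure can be reproduced. The statistical analysis plan was not available here; if it carries the same sentence, it needs the same change.

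The cost is a one-sentence correction. No additional participants and no change to the design or analysis are needed.

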### Training and certification

Clinical staff will be offered web-based training and certification prior to caring for trial participants. As this is a pragmatic trial, a specific certification rate will not be required before a neonatal intensive care unit can participate in the trial. However, the aim is to achieve the highest certification possible, at least 70% certification proportion in all participating neonatal intensive care units within the first 3 months of inclusion.

Since the web-based training and certification program is a trial quality measure to ensure quality of data and patient care, data on certification rates will be collected and published in a paper investigating the development and implementation of the web-based training and certification program for the SafeBoosC-IIIv trial. The principal investigator at each neonatal intensive care unit is responsible for listing relevant clinical staff who are expected to use the web-based training and certification program, as well as providing trial information, supervision, and support before and during trial conduct.

### Safety

An independent data monitoring and safety committee (DMSC) will be established to monitor mortality and neonatal morbidities at 28 days of life, including serious adverse reactions and serious adverse events. In the SafeBoosC-IIIv trial, serious adverse reactions will be defined as any adverse reaction to the experimental intervention that results in death, is life-threatening, requires hospitalisation or prolongation of existing hospitalisation, and results in persistent or significant disability or incapacity [18], including physical mishaps associated with managing the oximeter and sensors and clinical mismanagement based on data from the cerebral oxygenation monitoring.

The charter for the DMSC will be written prior to inclusion of participants and prior to any analysis.

### Data management

The Copenhagen Trial Unit will provide central, web-based data entry in the electronic case report form (eCRF) using OpenClinica®, an open-source data management environment that was also used for the SafeBoosC-II and SafeBoosC-III trials [19]. The parent report system will use RedCap as developed for the SafeBoosC-III 2-year follow-up study. Data will be managed and stored in line with approval by the Knowledge Centre on Data Protection Compliance, the Capital Region of Denmark.

### Monitoring

Central data monitoring will be performed by the trial manager, the coordinating investigator, and the Copenhagen Trial Unit. Monthly central checks will focus on recruitment to the trial, the quality, completeness, and timeliness of data entry in the electronic case report forms (eCRF). The central data monitoring will be conducted as described by Harboe Olsen et al. [20].

Local Good Clinical Practice monitoring will be done according to the International Conference on Harmonization’s Good Clinical Practice guideline [18]. The following will be monitored locally: all participants for the existence of a clinical file, existence of documented informed consent, and entry of trial participation in clinical files. Source checks will be done for group allocation and survival or death at 28 days of life. The maintenance of delegation and screening logs will be checked.

A screening log will be implemented. All mechanically ventilated infants who are not included will be classified according to cause, date, and counted. The data will be published in the final publication.

### Ethical considerations

Due to the pathophysiology of newborns, the question about cerebral oximetry in mechanical ventilated newborns can only be answered by a trial in this vulnerable population. Currently, there is variation in clinical practice and genuine uncertainty over whether cerebral oximetry is beneficial. There are risks in terms of skin injury and costs in terms of staff time and money for equipment.

The protocol has been approved by the Danish Ethics Committee (H-21071684: July 2022). All neonatal intensive care units must have their eligibility confirmed and the protocol should be approved by the relevant ethics committee before randomisation can begin. All the interventions that are suggested in the SafeBoosC treatment guideline are commonly used in this patient group, and cerebral oximetry is already in routine use in many neonatal intensive care units around the world. Therefore, the methods used to obtain informed consent by parents may be decided by the nationally or locally investigator as prior, opt-out, deferred, or combinations of these methods if it is approved by the ethics committee.

